##### 4.1.1.2 Secondary variables

Secondary variables will be the assessment of pain over the course of the 6-month treatment and healing process, the assessment of pain associated with ultrasound (pre- ultrasound to post-ultrasound pain assessments per visit), surface temperature changes related to healing using a thermal imaging camera, and judgment of independent reviewers regarding the correlation of the cosmesis score to the multiscale prediction model.

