#### 4.1.2 Number of subjects

Up to 15 de novo breast cancer subjects will be enrolled in order to allow for early drop-outs resulting in 12 evaluable cases.

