## 7 Statistical analysis plan

### 7.1.1 Sample size

This single-center study will enroll up to 15 de novo breast conserving therapy subjects. This is a prospective, pilot, observational study. Subjects withdrawn from the study cannot re-enter. Up to 3 patients, if withdrawn prior to week 6, will be replaced. Twelve subjects will be considered

evaluable if they complete up to visit 5 and will be considered completers if they complete all study visits and procedures.

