### 7.1.2 Preliminary Data Analysis Plan

Evaluable subjects will have completed a minimum of 5 visits (week 6). Descriptive statistics will be used to summarize the demographic and clinical characteristics of subjects. Changes at the end of study from baseline will be evaluated using chi-square for categorical variables and Kruskal-Wallis for continuous variables.

Receiver operator characteristic curves will be used to explore the sensitivity of the multiscale model to the outcome.

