### 7.1.3 Evaluation criteria:

- The primary outcome measure will be
- Qualitative:
  - confirmation that relative size of the lumpectomy to the breast, tissue composition ratio of fat versus glandular, and location of the tumor will provide a qualitative grading of the potential cosmetic outcome.
  - correlation of the wound edge shape to mechanical stress
  - correlation of volume loss due to healing to cosmesis outcome.
- Quantitative: a combined score of the correlation between three measured processes (lumpectomy dimensions, lumpectomy healing process, surface contour changes) and the predicted outcomes from the multiscale model measured/assessed at weeks 10 and 26 postsurgery with a mean accuracy rate of  $\geq 60\%$ .
- Secondary outcome measures will include postsurgery:
  - the proportion of subjects experiencing pain  $\geq 8$  on more than one measurement post operatively and the relationship of pain to the accuracy of the multiscale model
  - the proportion of subjects experiencing increased pain ( $\geq 3$  unit increase) pre to post ultrasound at each visit to determine the possible invasiveness of these multiple post-surgery ultrasounds
  - detection of changes in the thermal image of the breast tissue related to inflammation and healing
  - the summary of the independent judgment (Harvard/NSABP/RTOG scale score) of cosmesis taken at weeks 10 and 26

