##### 9.4.1.2 Ultrasound

There are no known long-term side effects of ultrasound. The ultrasound procedure is not expected to cause discomfort to the patient but pain will be assessed/quantified pre/post ultrasound at each visit in order to capture this information. If at any time the subject expresses the desire to discontinue the ultrasound procedure, they will be allowed to discontinue the procedure.

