#### 9.4.3 Risk:Benefit ratio

The benefit:risk for participants in this study is considered mildly negative given that the subject is not expected to benefit directly from the research and might experience mild pain during the ultrasound procedures. Participating in the study may be perceived as an inconvenience to some patients.

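### Section 7.1.3 summarises scan-related pain only as the proportion of women rising 3 or more units, so a small rise shared by most of 12 women can look absent or rare

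*Protocol*

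**What the plan says.** Section 4.1.1.2 of the protocol lists as a secondary variable "the assessment of pain associated with ultrasound (pre- ultrasound to post-ultrasound pain assessments per visit"), with no cut-off. Section 7.1.3 turns this into a secondary outcome: the proportion of subjects with a rise of at least 3 units, "pre to post ultrasound at each visit to determine the possible invasiveness of these multiple post-surgery ultrasounds". The appendix pain scale runs from 0 to 10, so the cut is 30% of the range. Scans, each with a score before and after, take place at visits 2 to 6 (sections 6.5, 6.6 and 6.8.1).

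On the size of effect expected, section 9.4.1.2 says the scan is "not expected to cause discomfort to the patient but pain will be assessed/quantified pre/post ultrasound at each visit". Section 9.4.3 adds that a woman "might experience mild pain during the ultrasound procedures".

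No other analysis in the protocol summarises the change around a scan:

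- Section 7.1.2 says "Changes at the end of study from baseline will be evaluated", which compares the end of the study with its start, not after a scan with before it. Its descriptive statistics are for demographic and clinical characteristics.
- The other pain outcome in 7.1.3, pain of 8 or more on more than one measurement, concerns pain level rather than change.

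Section 4.1.2 allows up to 15 enrolled subjects "in order to allow for early drop-outs resulting in 12 evaluable cases".

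**The concern.** The outcome is meant to show whether repeated scanning of a healing breast is a burden, and the protocol foresees mild pain at most. A 3-unit cut gives no weight to a 1- or 2-unit rise, however many women have it. The protocol does not say what score is mild, so some mild pain could still reach 3 units, but small rises are plausible.

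Two misreadings follow. A modest rise shared by most women can be reported as no or almost no events. Conversely, a few events can arise from ordinary scatter when there is no average rise, because women whose pain falls are not set against those whose pain rises. The proportion alone cannot separate these cases, although the paired scores that could are already collected. At stake is the accuracy of the pilot's statement about scan burden. The primary endpoint is not affected.

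**Working it through.** **Inputs from the protocol.** 12 evaluable women (15 enrolled less up to 3 replaced: 15 − 3 = 12; sections 4.1.2 and 7.1.1), five scan visits, a 0-10 scale, and a cut at a rise of 3. The protocol gives no power, expected proportion, mean or SD for this outcome, so there is no figure to reproduce.

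**Without assumptions.** If all 12 women rise by 1 or 2 units at a visit, the outcome is 0/12. The exact 95% upper limit is 1 − 0.025^(1/12) = 26%. A two-sided sign test on the same data gives 2 × 0.5^12 = 0.0005.

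**With assumptions.** Take the change (after minus before) as normal with mean m and SD s, rounded to whole units. Then:

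- p = P(rise ≥ 3) = 1 − Φ((2.5 − m)/s)
- expected count = 12p
- P(0 of 12) = (1 − p)^12
- P(at most 1 of 12) = (1 − p)^12 + 12p(1 − p)^11

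For m = 1, s = 1:

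- p = 1 − Φ(1.5) = 0.067, so 12p = 0.80.
- P(0) = 0.933^12 = 0.44, and P(at most 1) = 0.81.
- The share rising by 1 or 2 is Φ(1.5) − Φ(−0.5) = 0.933 − 0.309 = 0.625, or 7.5 of 12 women who are not counted.

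The last column below is the simulated chance, for 12 rounded changes, that the paired-t 95% CI for the mean lies wholly above zero. At s = 1 its half-width averages about 0.65 units.

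| Mean rise | SD | p | Expected of 12 | P(0) | P(at most 1) | Paired CI above 0 |
|---|---|---|---|---|---|---|
| 0.5 | 1 | 0.023 | 0.27 | 76% | 97% | 32% |
| 1 | 1 | 0.067 | 0.80 | 44% | 81% | 85% |
| 1.5 | 1 | 0.159 | 1.90 | 13% | 41% | 99% |
| 2 | 1 | 0.309 | 3.70 | 1% | 8% | 100% |
| 1 | 2 | 0.227 | 2.72 | 5% | 21% | about 35% |

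**Choice of cut.** If changes are treated as continuous and cut at 3.0 instead of 2.5, m = 1, s = 1 gives p = 0.023, P(0) = 0.76 and P(at most 1) = 0.97. The whole-unit figures are therefore the milder version.

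**Scatter alone.** For m = 0, s = 2, p = 1 − Φ(1.25) = 0.106. The expected count is 12 × 0.106 = 1.27, and P(at least 1) = 1 − 0.894^12 = 74%. That is more expected events than a consistent 1-unit rise gives at s = 1 (0.80).

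**Five visits, m = 1, s = 1.** If a woman's changes are independent across visits, P(at most 1 at every visit) = 0.811^5 = 35% and P(no event in 60 scans) = 0.436^5 = 1.6%. Simulation with a shared effect per woman gives the rest.

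| Within-woman correlation | At most 1 event at every visit | No event in 60 scans |
|---|---|---|
| 0 | 35% | 1.6% |
| 0.5 | 45% | 6% |
| 0.8 | about 57% | 14% |
| 1 | 81% | 44% |

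**The case against.** A prespecified responder cut is legitimate, and counting women with a marked rise answers a question about invasiveness directly. Whether a shared 1-unit rise matters is a clinical judgement. The list in 7.1.3 is worded as open, the variable in 4.1.1.2 carries no cut, and a separate analysis plan could add a mean or median. Mild events can also be recorded as adverse events under section 9.1. All of this stands as a reason to keep the cut and to rate the point low. It does not restore the information that the stated outcome discards: the protocol's own statistical section gives the dichotomy as the measure for this purpose, and adverse event reports are not a paired summary.

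The numbers also have limits. They rest on assumed means and SDs. The normal model ignores the floor of the scale: a woman at 0 before the scan cannot fall, which makes the scatter-only example less realistic where pain before the scan is low. The protocol has no rule that 0 or 1 event means the scans are harmless, so setting P(at most 1) beside the paired interval compares what each summary tends to show, not two decision rules. Over all 60 scans a complete absence of events is unlikely unless a woman's changes are highly correlated across visits, so rare is the more robust description than absent. Finally, the loss comes mainly from the cut, which ignores rises below 3 at any sample size; having 12 women makes a low true proportion likely to show as 0 or 1.

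**Conclusion.** The concern holds as a minor, cheap improvement. That rises of 1 or 2 units are uncounted follows from the definition and needs no assumption. How often this would hide a shared rise does depend on assumptions. Masking is clear for mean rises of about 0.5 to 1 unit with SD about 1, less marked at 1.5, and mostly gone at 2. The paired summary is clearly the more informative at means of 1 to 1.5 with SD 1. At a mean of 0.5, or with SD 2 at a mean of 1, its interval would exclude zero only about a third of the time. It would still show the direction and size of the change, which the proportion does not.

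**What to change.** In section 7.1.3, keep the proportion with a rise of 3 or more units and add one sentence along these lines: at each visit the within-woman change in pain score (after minus before ultrasound) will also be reported as a mean or median with a 95% confidence interval, together with the number of women who had a fall, no change, and a rise of 1, of 2, and of 3 or more units.

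This needs no extra visit, score, form or staff, because the paired scores are already taken at visits 2 to 6. Scan-related pain may look less favourable than under the proportion alone, and the five intervals should be read as descriptive, not as five tests.

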##### 4.1.1.1 Primary variables

The primary variables will be surface contour captured by the 3-dimensional 180° camera, lumpectomy dimensions captured by ultrasound, predicted surface contour and predicted lumpectomy dimensions from the multiscale model.

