## **6.8 Judging**

Breast cosmesis will also be assessed using the 4-point Harvard/NSABP/RTOG cosmesis criteria scale (Appendix) and judged by two independent surgeons not involved in the care of the patient or the study. Judging will occur at baseline (after surgery) and at week 10 and week 26.

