### 6.8.1 Sequence of events

| Month               |          |   | 1 |    |    |    | 3 | 6 |    |
|----------------------------|----------|---|----------|----|----|----|----------|----------|----|
| Week                |          |   | 1        | 3  | 6  | 10 | 12       | 24       | 26 |
| Visit day           | -21 to 0 |   | 1        | 2  | 3  |    | 4        | 5        |    |
| Visit window (days) | -21      |   | 0        | ±7 | ±7 |    | ±7       | ±7       |    |
| Visit number        | 1        |   | 2        | 3  | 4  |    | 5        | 6        |    |
| Parameter           |          |   |          |    |    |    |          |          |    |
| Informed consent           | X        |   |          |    |    |    |          |          |    |
| 3-D SI*                    | X        |   | X        |    | X  |    |          | X        |    |
| Surgery                    |          | X |          |    |    |    |          |          |    |
| Thermal image              |          |   | X        | X  | X  |    | X        | X        |    |
| Ultrasound†                |          |   | X        | X  | X  |    | X        | X        |    |
| Radiation therapy          |          |   | X        | X  | X  |    |          |          |    |
| Pain scale score‡          | X        |   | XX       | XX | XX |    | XX       | XX       |    |
| Cosmesis judging§          |          |   | X        |    |    | X  |          |          | X  |

\*3-dimensional 180° camera surface imaging

†Breast ultrasound of the tumor / lumpectomy area

‡Performed pre and post ultrasound

§Independent assessment of cosmesis using the Harvard/NSABP/RTOG cosmesis criteria and comparison to multiscale model

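### The protocol twice defines judged cosmesis as a comparison with the multiscale model, but the matching secondary outcome in 7.1.3 only summarises the grades

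*Protocol*

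**What the plan says.** Four places in the protocol describe the judged-cosmesis item.

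- **4.1.1.2 (Secondary variables)** lists the "judgment of independent reviewers regarding the correlation of the cosmesis score to the multiscale prediction model".
- **6.8 (Judging)** has breast appearance graded on the 4-point Harvard/NSABP/RTOG scale and "judged by two independent surgeons not involved in the care of the patient or the study". It does not mention the model. On timing: "Judging will occur at baseline (after surgery) and at week 10 and week 26".
- **6.8.1 (schedule footnote)** explains the cosmesis row as "Independent assessment of cosmesis using the Harvard/NSABP/RTOG cosmesis criteria and comparison to multiscale model".
- **7.1.3 (Evaluation criteria)** gives the secondary outcome as "the summary of the independent judgment (Harvard/NSABP/RTOG scale score) of cosmesis taken at weeks 10 and 26".

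Three other places bear on it. Section 4.1.1.1 names the model's outputs as "predicted surface contour and predicted lumpectomy dimensions from the multiscale model". The quantitative primary measure in 7.1.3 is built from "three measured processes (lumpectomy dimensions, lumpectomy healing process, surface contour changes) and the predicted outcomes from the multiscale model". The qualitative primary items in 7.1.3 include the "correlation of volume loss due to healing to cosmesis outcome". Section 7.1.2 also plans ROC curves for the model, but does not say which outcome they use.

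**The concern.** The purpose in section 2.1 is to test the model's predictive validity, and the rationale in 1.2 looks ahead to patients for whom a cosmetic defect would be predicted before surgery. A grade of appearance by two outside surgeons is the most direct human check on that use, and two places in the protocol say it will be compared with the model. The section that fixes the outcomes leaves the comparison out.

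A table of grades, for example 9 women excellent or good and 3 fair or poor (invented counts), describes the result of surgery and radiotherapy. It would look the same whether the model had picked out the 3 or missed all of them. The grades would be collected twice over, by two surgeons, without a stated use as a test of the model.

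It is also unclear who makes the comparison. Section 4.1.1.2 reads as if the outside surgeons judge the correlation themselves, while 6.8 asks them only to grade.

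**Working it through.** **1. The protocol's own figures.** No figure is in dispute. Enrollment reproduces: 12 evaluable (4.1.2) + 3 replacements (7.1.1) = 15. The protocol gives no power calculation for this item.

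**2. The sections side by side.**

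| Place | Judged grade named? | Compared with the model? |
|---|---|---|
| 4.1.1.2 | Yes, as the cosmesis score | Yes, apparently by the surgeons |
| 6.8 | Yes | Not mentioned |
| 6.8.1 footnote | Yes | Yes, method not stated |
| 7.1.3 secondary, cosmesis | Yes | No |
| 7.1.3 primary, quantitative | No (dimensions, healing, contour) | Yes |
| 7.1.3 primary, qualitative | Cosmesis, but not the surgeons' grade | No model output named |
| 7.1.2 ROC | Outcome not named | Yes |

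The comparison appears in 4.1.1.2 and the footnote. No analysis statement in section 7 names both the grade and the model. The pain item in the same secondary list does carry a link to the model's accuracy; the cosmesis item does not.

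**3. What the model offers for comparison.** Section 4.1.1.1 names a predicted contour and predicted lumpectomy dimensions. Neither is a single number that can be ranked against a 4-point grade, so one has to be derived.

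**4. What the comparison could show.** Inputs: n = 12 (4.1.2); an observed correlation r = 0.6, which is an assumption for illustration. The Fisher transform is z = atanh(0.6) = 0.693.

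- Pearson standard error, 1/√(n − 3) = 1/3: 0.693 ± 1.96/3 = 0.040 to 1.346. Back-transformed: 0.04 to 0.87.
- Spearman-adjusted standard error, √[(1 + r²/2)/(n − 3)] = √(1.18/9) = 0.362: 0.693 ± 0.710 = −0.017 to 1.403. Back-transformed: about −0.02 to 0.89.

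The second interval is the relevant one for a rank correlation, and it includes zero. Ties on a 4-point scale make either formula approximate.

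**5. Fewer week 26 grades.** Sections 7.1.1 and 7.1.2 count a woman as evaluable well before week 26, so 12 evaluable women need not give 12 final grades. If 10 did (an assumption): √(1.18/7) = 0.411, and 0.693 ± 0.805 = −0.112 to 1.498, or about −0.11 to 0.90.

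**6. Surgeon disagreement.** Let R be the reliability of one surgeon's grade. The protocol gives no value; R = 0.5, range 0.4 to 0.7, is assumed. The highest correlation a perfect predictor could reach is √R with one surgeon's grade and √[2R/(1 + R)] with the mean of two.

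| R | One surgeon | Mean of two |
|---|---|---|
| 0.4 | 0.63 | 0.76 |
| 0.5 | 0.71 | 0.82 |
| 0.7 | 0.84 | 0.91 |

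The agreement coefficient is therefore not itself the ceiling: R = 0.5 allows 0.71 or 0.82. These formulas belong to Pearson correlation and an intraclass coefficient, so for ordinal ranks they are only a guide.

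**The case against.** The other side has four arguments.

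- **Cosmesis is analysed elsewhere in 7.1.3.** The qualitative primary items relate volume loss, lumpectomy size relative to the breast, tissue composition and tumor location to cosmetic outcome, and 1.1 treats tumor size and location as inputs to the model work. This stands. A reader might infer that 7.1.3 does nothing with cosmesis but tabulate it, and the document does not support that. These items still name neither the surgeons' grade nor a model output, so they do not close the gap.
- **The ROC analysis may be the missing comparison.** An ROC curve needs a two-class outcome, and a split of the 4-point grade is a natural candidate. The secondary list is also worded as open, and 4.1.1.2 and the footnote still commit the study to the comparison. This too stands. A reader might conclude that the question will go unanswered, but all that can be shown is that the analysis is unspecified.
- **The details belong in a statistical analysis plan.** The choice of statistic and the way two readings are combined could well sit there, and their absence is not held against the protocol. The disagreement over what the outcome is lies in the protocol itself.
- **It is one secondary item in a descriptive pilot of 12.** That is true. It limits the weight of the point, and the quantitative primary measure is unaffected.

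**Conclusion.** The point holds as an inconsistency in the definition of a secondary outcome. Sections 4.1.1.2 and the footnote in 6.8.1 make judged cosmesis a comparison with the model; the 7.1.3 outcome keeps only the grades; no other section explicitly supplies the comparison. This rests on the wording alone and needs no assumption.

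The figures show only what the missing comparison could deliver. With an assumed r of 0.6 the interval runs from near zero to near 0.9 at n = 12, so it could not confirm or refute the model. It would still tell the reader something about the model, which a summary of grades does not. The point is worth correcting because it bears on the stated purpose and the data are already planned.

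**What to change.** Reconcile 4.1.1.2, 6.8, the 6.8.1 footnote and 7.1.3 around one definition.

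- **7.1.3, cosmesis item.** Replace the summary with a rank association (Kendall tau-b or Spearman, with an exact or bootstrap 95% interval) between a single deformity measure derived from the model-predicted surface contour and the mean of the two surgeons' grades at week 26. Week 10 is supportive. The grade distribution can be shown beside it.
- **Deformity measure.** Define it in writing before anyone involved sees the grades.
- **4.1.1.2, 6.8 and the footnote.** State that the surgeons only grade and that the analyst computes the association. The surgeons should not be asked to judge the correlation.
- **Agreement.** Report weighted kappa between the two surgeons as context, and do not label it the ceiling.
- **7.1.2.** Name the outcome for the ROC curves. If it is the grade, give the cut.
- **Numbers.** Report how many women have week 26 grades and call the result descriptive.

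The cost is protocol wording, the work of defining one deformity measure, and a short analysis. No new visits, images or readers are needed. The drawback is that a wide interval, probably including zero unless the association is strong, has to be reported.

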## 8 Removal of Subject from Study

### 8.1 Discontinuation of Study

The Principal Investigator reserves the right to discontinue this study at any time. Should this occur, the appropriate authorities (eg, Institutional Review Board) will be informed, and the reason for discontinuation will be indicated in the Case Report Form (CRF). A study termination CRF must be completed.

## 8.2 Withdrawal from Study

### 8.2.1 Discontinuation of Study Procedures

The Principal Investigator will discontinue testing a subject if she believes it is in the subject's best interest. When a subject discontinues receiving imaging studies, the subject will be followed according to the standard of care. The date that the subject discontinues the study will be recorded.

### 8.2.2 Early Withdrawal/Study Termination

Subjects who enroll in the protocol and withdraw, at any time for any reason, before visit 5 are considered early withdrawals and will be replaced up to a maximum of 3 withdrawals. A complete set of data including reason for withdrawal will be collected on each subject through the time interval of withdrawal.

Subject tracking should include, but is not limited to: (1) at least 3 attempts to contact subjects by phone, (2) at least 3 attempts to contact subjects through the names subjects authorized, and (3) 1 attempt to contact subjects by registered letter. Documentation of all contact attempts should be retained in the source documents for the subject, including a copy of the letter sent and the returned receipt of mailing.

Subjects experiencing adverse reactions should be followed until the reaction has resolved, stabilized, or is otherwise explained.

